– Rotation of the tibial component: angle between the tibial tubercle axis (axis between the geometric center of the proximal tibial plateau and the tip of the tubercle) and the tibial component angle (anterior-posterior line through the tibial component). Normal rotation of the tibial component is considered 18° endorotation [30]. Endorotation of the tibial component will be shown as a positive (+) angle and exorotation of the tibial component will be shown as a negative (-) angle. An angle of >3° endorotation or exorotation will be considered an outlier.

Prosthetic alignment in the coronal and sagittal planes will be measured using postoperative coronal and sagittal X-rays of the operated leg. These lower-limb X-rays are obtained using the EOS system (Biospace Imaging, Paris, France) [28] EOS 2D images will be used for measuring alignment. For the intervention group, standard coronal and sagittal X-rays will be taken postoperatively as part of the standard operation protocol. For the historical control group, standard coronal and sagittal X-rays have already been taken postoperatively.

Angles measured for coronal and sagittal alignment are:

– Mechanical angle of the leg (HKA): Angle between the line from the femoral head to the center of the knee and the line from the center of the ankle to the center of the knee in coronal plane.

– Mechanical lateral distal-femoral angle (mLDFA): Angle between the mechanical axis of the femur and the articular surface of the femoral part of the prosthesis in coronal plane.

– Mechanical medial proximal tibial angle (mMPTA): Angle between the mechanical axis of the tibia and the articular surface of the tibial part of the prosthesis in coronal plane.

– Anatomical proximal posterior tibial angle (aPPTA): Angle between the mechanical axis of the tibia and the articular surface of the tibial part of the prosthesis in sagittal plane. Downslope of the design of Nexgen prostheses is 7°, and this angle is considered the normal aPPTA.

– For the mechanical axis of the leg, mLDFA, mMPTA and aPPTA a generally accepted outlier cut-off of +/-3° will be applied in this study [31-34].

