### Sample size

The hypothesis is that the use of CAS leads to fewer outliers in prosthetic alignment compared to the use of mechanical alignment guides during rTKA. Primary outcome measure will be rotational prosthetic alignment. When using the conventional operation technique, around 25% of the knees is considered a radiological outlier. Therefore, a P2 value of 0.75 was chosen [21,36]. Previous research has shown that the use of CAS in TKA decreases the number of outliers by 17-30% [21,37,38]. When a 20% decrease in outliers is expected in the CAS group compared to the control group with P1 = 0.95, P2 = 0.75, power = 80% and alpha = 0.05, 44 patients per group are needed.

Since 2008 a total of amount of 21-30 rTKAs have been performed each year at UMCG, and an increase is expected. As a result of that, the possibility is expected of including 44 patients in the intervention group between September 2012 and September 2015. Inclusion of 44 patients in the historical control group is not expected to be a problem, as 165 rTKAs were performed between January 2002 and April 2012.

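### As written, the tibial rotation outlier rule is centred on 0° although the protocol's stated normal is 18° endorotation, so the tibial outlier count would be invalid if the rule were applied literally

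*Protocol article*

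**What the plan says.** All of the text at issue is in the protocol article.

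- *Radiographic evaluation*, tibial component. Rotation is the angle between the tibial tubercle axis and the anterior-posterior line through the component, so 0° means that the two lines are parallel. The reference value is "Normal rotation of the tibial component is considered 18° endorotation". The sign convention is "Endorotation of the tibial component will be shown as a positive (+) angle and exorotation of the tibial component will be shown as a negative (-) angle". The outlier rule follows directly: "An angle of >3° endorotation or exorotation will be considered an outlier".
- *Radiographic evaluation*, femoral component. The outlier sentence is identical, but no non-zero normal is given for the femoral angle.
- *Radiographic evaluation*, coronal and sagittal angles. The wording differs here: "a generally accepted outlier cut-off of +/-3° will be applied in this study".
- *Sample size*. "Primary outcome measure will be rotational prosthetic alignment". The hypothesis is that computer-assisted surgery gives fewer outliers. The calculation uses non-outlier proportions of 0.95 and 0.75, that is, 5% versus 25% outliers.
- *Statistical analysis*. Differences in alignment between the groups are to be tested with the Mann-Whitney U-test.

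**The concern.** Normal rotation, sign convention and outlier rule stand in consecutive sentences and share one scale, yet the rule excludes the normal value. Nothing says that 18° is subtracted first, or that the 3° is a deviation from normal. In the 18° sentence, endorotation is measured from the tubercle axis. To read the same word two sentences later as measured from 18° requires a change of zero that is not stated. The sentence looks as if it was carried over from the femoral angle without being re-centred.

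At stake is the tibial outlier count. Femoral and tibial rotation are determined separately, so the tibial angle is one of the two measures behind the primary outcome, and the hypothesis is expressed in outliers. An assessor who follows the text and one who follows the probable intention would disagree on every component that either of them accepts.

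**Working it through.** **The plan's own figure.** The target is 44 per group from P1 = 0.95, P2 = 0.75, 80% power and alpha 0.05. The two-sided arcsine formula is n = 2[(1.960 + 0.842)/h]², with h = 2·asin(√0.95) − 2·asin(√0.75) = 0.596. It gives n ≈ 44.2, which agrees with the plan apart from rounding up to 45. Other formulas give other values (the pooled two-sided formula gives 49), but that is a separate matter. P1 and P2 are assumed rates, so n does not depend on how the tibial rule is worded.

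**Classification under the two readings.** Inputs are the protocol's normal (+18°), its sign convention and its 3° cut-off.

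| Measured angle | As written, \|angle\| > 3° | Centred on normal, \|angle − 18°\| > 3° |
|---|---|---|
| −3° | not an outlier | outlier |
| 0° | not an outlier | outlier |
| +3° | not an outlier | outlier |
| +15° | outlier | not an outlier |
| +18° | outlier | not an outlier |
| +21° | outlier | not an outlier |

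The accepted windows are −3° to +3° and +15° to +21°. They are disjoint, so no component is acceptable under both. This step needs no distributional assumption.

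**Illustration of size.** The documents give no mean or SD for the tibial angle. I assume a normal distribution with mean 18° and vary the SD, s. The share flagged by the written rule is

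1 − [Φ((3 − 18)/s) − Φ((−3 − 18)/s)].

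The lowest SD is chosen so that the 18°-centred rule gives the planned 25%: s = 3/z(0.875) = 3/1.150 = 2.61°. This borrows a rate that the protocol states for knees, not for tibial rotation. The larger SDs are arbitrary and are there to see whether a wide spread would rescue the rule.

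| Assumed SD | Flagged as written | Flagged if centred on 18° |
|---|---|---|
| 2.61° | >99.99% | 25.0% |
| 4° | 99.99% | 45.3% |
| 5° | 99.9% | 54.9% |
| 8° | 97.4% | 70.8% |
| 10° | 95.1% | 76.4% |

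For SD 10° the written rule gives 1 − [Φ(−1.5) − Φ(−2.1)] = 1 − (0.0668 − 0.0179) = 0.951. Across this range the written rule never comes near 25% or 5%, and the few components it accepts lie at least 15° from the stated normal.

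**The case against.** The best defence is context. The normal value comes just before the rule. In the same section a 3° cut-off is applied to the sagittal tibial angle, whose normal is given as 7°, and to coronal component angles for which no target is stated; there it makes sense only as a tolerance around a target. The planning rates of 25% and 5% also cannot arise for the tibia under the literal rule if components lie near 18°. The protocol further refers to a cited CT method, which may report deviation from normal; that source is not available here. I accept that 3° either side of 18° is probably what was meant. The defect is that the text states something else.

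Three stronger readings are tempting, and the documents do not support them.

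- *That the whole primary comparison is uninformative or reversed.* The test named for alignment is the Mann-Whitney U-test. If it is run on the measured angles, it does not use the cut-off. The femoral rule is not affected either. The damage is confined to the dichotomised tibial result.
- *That half of the primary outcome is lost.* The protocol gives no weighting of the two components, and a partial revision contributes only the part that was revised.
- *That the sagittal tibial angle has the same fault.* It is defined as an angle between axis and surface, which for a 7° downslope would be 90 − 7 = 83°, yet the protocol says: "Downslope of the design of Nexgen prostheses is 7°, and this angle is considered the normal aPPTA". This is a fixed 90° change of notation. A slope of 4° to 10° is the same set of knees as an angle of 80° to 86°, so no knee changes outlier status.

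**Conclusion.** The point holds for the tibial outlier definition. As written, the rule contradicts the protocol's own normal value and classifies a component at that normal as malaligned. The contradiction follows from the text alone. The illustrated size, about 95% to more than 99.9% flagged, rests on assumed normality, a mean of 18° and SDs of 2.6° to 10°. It shows how the literal rule would behave and is not a prediction of the trial's results.

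The consequence is conditional: if the sentence is applied literally, the tibial outlier count is invalid and cannot address the hypothesis of fewer outliers. The documents do not show that it would be applied that way. Because the hypothesis and sample size are framed in outliers for rotational alignment, the wording should still be corrected and not left to the assessor's interpretation.

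**What to change.** In *Radiographic evaluation*, replace the tibial outlier sentence with one that names its reference: a tibial component is a rotational outlier if |measured angle − 18°| > 3°, that is, outside 15° to 21° endorotation. This uses only the normal value and the cut-off already in the protocol. Make the change before any images are classified, and apply the same definition in both groups.

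The cost is one sentence. No new scans or measurements are needed, and the femoral rule and the planned 44 per group stay as they are.

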## Methods/Design

### Study design

A prospective clinical intervention study with use of a historical control group will be conducted. In the prospective intervention group patients will undergo rTKA using CAS. These surgeries will take place between September 2012 and September 2015. The historical control group will consist of patients who underwent rTKA between January 2002 and April 2012. The intervention and control groups will be matched according to gender and type of revision prosthesis. The study design, procedures and informed consent are approved by the Medical Ethics Committee of University Medical Center Groningen (UMCG).

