### Radiographic evaluation

Rotational prosthetic alignment will be measured on a CT-scan of the operated leg. For evaluation of alignment in the coronal and sagittal planes a new imaging device, called the EOS system (Biospace Imaging, Paris, France) [28], will be used. This device is characterized by a reduction in radiation (800-1000 times less than for CT-scan and 10 times less than conventional X-ray) [28,29]. Reason for this is the use of an innovative technology called fast gaseous particle detectors, invented by George Charpak (which earned him the Nobel prize in physics in 1992). The EOS imaging device uses two orthogonal sources of radiation and linear detectors that are coupled together. These sources move up and down along the patient, producing an anterior-posterior and lateral image at the same time while the patient is in weightbearing position. This is a different technique than conventional radiograph systems, where beams are divergent in horizontal and vertical plane.

Of the patients in the intervention group, a CT-scan of the operated leg will be made postoperatively during the visits at the outpatient clinic. Patients included in the historical control group have already undergone the standard surgical technique for rTKA. A CT-scan of the operated leg will be made the next time the patient visits the outpatient clinic of the Orthopedic Department for follow-up of the rTKA.

For evaluation of rotational prosthetic alignment, rotation of the femoral and tibial components will be determined separately according to the Berger CT protocol [30]. Angles measured for rotational alignment are:

– Condylar twist angle for rotation of the femoral component: angle between the epicondylar axis and the prosthetic posterior condylar axis (inner border of posterior cut). Endorotation of the femoral component will be shown as a positive (+) angle and exorotation of the femoral component will be shown as a negative (-) angle. An angle of >3° endorotation or exorotation will be considered an outlier.

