The canal-filling ratio (CFR) will be determined in both the intervention and control groups to assess whether the stems are canal-filling. The CFR will be measured on the coronal and sagittal EOS images as described by Parsley et al. [35]. The stem diameter and endosteal diameter will be measured at the stem tip. The CFR will be calculated by dividing the stem diameter by the endosteal diameter. A stem is considered to be canal-filling when the CFR is ≥0.85 [35].

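### Coronal and sagittal angles are to be read on EOS images, yet controls rely on X-rays already taken after operations from 2002 to 2012: the plan must say which device produced them, because imaging method may follow group in these secondary comparisons

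*Protocol article*

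**What the plan says.** All statements are in the protocol article.

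- **Device.** Radiographic evaluation opens with "For evaluation of alignment in the coronal and sagittal planes a new imaging device, called the EOS system". Of the X-rays used for the angles it then says "These lower-limb X-rays are obtained using the EOS system", with no group exempted. Of the canal-filling ratio (CFR), which both groups receive, it says "The CFR will be measured on the coronal and sagittal EOS images".
- **How the device differs.** The same section says of EOS: "This is a different technique than conventional radiograph systems, where beams are divergent in horizontal and vertical plane".
- **Source of the images.** CAS patients are imaged prospectively: "For the intervention group, standard coronal and sagittal X-rays will be taken postoperatively as part of the standard operation protocol". Controls are not: "For the historical control group, standard coronal and sagittal X-rays have already been taken postoperatively".
- **Dates.** Under Study design: "The historical control group will consist of patients who underwent rTKA between January 2002 and April 2012". For the CAS group: "These surgeries will take place between September 2012 and September 2015".
- **New imaging of controls.** The only examination described is the CT at the next follow-up visit, which serves the rotational outcome.
- **Analysis.** Statistical analysis assigns the Mann-Whitney U-test to rotational, coronal and sagittal alignment. Matching is on gender and type of revision prosthesis. Imaging device and image date are not among the variables listed under Study procedures.

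**The concern.** The statements are hard to hold together. A device presented as new is to supply every coronal and sagittal image, yet the control images already exist and belong to operations going back more than ten years. The text does not say when EOS came into use at the centre, whether every control image is an EOS image, or what happens to a knee that has only a conventional film.

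All CAS operations come after all control operations. If some control films are conventional, device and group are therefore aligned, and the protocol's own description of the beam geometry gives reason to expect that readings could differ. With a fixed ±3° cut-off, a difference in bias or precision between devices would change the control outlier rate with no difference in surgery. Neither the matching nor the planned test would remove it. At stake is whether a difference in the four secondary angles can be credited to CAS.

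**Working it through.** **Step 1: what is exposed.** The protocol gives no figure on this point to reproduce. Its 44 per group was set for outliers in the rotational outcome (0.95 versus 0.75, 80% power, alpha 0.05). The two-sided arcsine formula gives 44.2, which agrees. It enters below only as the group size.

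- Rotation (primary): CT in both groups, so not exposed.
- HKA, mLDFA, mMPTA, aPPTA: EOS is prescribed and control films already exist, so exposed wherever a control film is not EOS.
- CFR: stem diameter divided by endosteal diameter, both at the stem tip. A common magnification m cancels, (m × stem)/(m × endosteal) = stem/endosteal, so CFR is little exposed.

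**Step 2: sensitivity of the outlier rate.** Inputs: the ±3° cut-off (Radiographic evaluation) and about 25% outliers with conventional technique (Sample size). The protocol does not tie the 25% to EOS or to these angles, so using it here is an assumption. So are normality and centring on target.

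- Implied SD: 3 / z(0.875) = 3 / 1.150 = 2.61°.
- With offset b and extra random error of SD e in control readings, s = √(2.61² + e²) and the outlier rate is 1 − [Φ((3 − b)/s) − Φ((−3 − b)/s)].

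| b | e | s | Apparent control outlier rate |
|---|---|---|---|
| 0 | 0 | 2.61 | 25.0% |
| 1° | 0 | 2.61 | 28.4% |
| 2° | 0 | 2.61 | 37.8% |
| 0 | 1° | 2.79 | 28.3% |
| 0 | 2° | 3.29 | 36.1% |

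These rows assume that every control film is non-EOS. If only half were (again an assumption), the offset rows would shrink to 25.0 + 0.5 × 3.4 = 26.7% and 25.0 + 0.5 × 12.8 = 31.4%.

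**Step 3: sensitivity of the planned test.** Simulation: 2000 runs, 44 per group, no true difference, two-sided 5% Mann-Whitney test. The Monte Carlo standard error at 5% is √(0.05 × 0.95 / 2000) ≈ 0.5 percentage points.

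| Control readings | Rejects, signed angles | Rejects, absolute deviations |
|---|---|---|
| no difference | 4.5% | 5.3% |
| offset 0.5° | 13.3% | 4.9% |
| offset 1° | 40.8% | 5.6% |
| offset 2° | 93.2% | 27.9% |
| extra SD 1° | 5.9% | 6.2% |
| extra SD 2° | 4.6% | 21.0% |

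A systematic offset is what harms a test on signed angles. Extra random error leaves that test near 5% and matters for outlier rates or, when large, for absolute deviations.

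**Step 4: room for selection.** Sample size counts 165 revisions in the control period for 44 places, or 165/44 = 3.75 per place before eligibility and matching. How many of these knees have EOS images is not stated.

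**The case against.** The strongest objection is that no sentence says any control image is non-EOS. Read literally, the section makes all the lower-limb X-rays EOS images. Nor does it date the control films: controls are still in follow-up, so a knee revised years ago could have a later EOS image, and a set of 44 with EOS images is not ruled out among 165 revisions. A condensed article may also leave the acquisition details to the full protocol. This stands so far as it goes: confounding is a strong inference, possibly partial, and not a stated fact. It does not remove the conflict, because the article itself fixes the image source for each group and the two descriptions do not fit without a further statement.

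Four stronger readings are tempting and are not supported:

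- **The main result is compromised.** It is not: rotation is read on CT in both groups.
- **CFR is affected like the angles.** It is a same-level ratio with its own 0.85 threshold, and the ±3° argument does not apply to it.
- **The 1-2° figures measure the bias.** They are assumed values, and the documents give no error between devices.
- **EOS images of controls should be taken at the CT visit.** That would be an additional procedure, and it would image some controls years after surgery while CAS patients are imaged postoperatively. It would exchange a possible device difference for a time-since-surgery difference.

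**Conclusion.** The concern holds in conditional form and for secondary outcomes only. The protocol prescribes EOS for the coronal and sagittal angles and for CFR, but it draws control images from an existing stock linked to operations from January 2002 to April 2012 and does not state the device. To the extent that those images are not EOS, device follows group for HKA, mLDFA, mMPTA and aPPTA, and the unadjusted test cannot tell it from a CAS effect.

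The size is unknown. Under the assumptions shown (normal angles centred on target, SD 2.61°, all control films non-EOS), an offset of 1-2° moves a 25% control outlier rate to 28-38%. Extra random error of SD 1-2° moves it to 28-36% without disturbing a signed-angle test. If every control image proves to be EOS, the device confounding disappears and only the wording needs correcting. The primary rotational comparison and its sample size are untouched in either case.

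**What to change.** 1. In Radiographic evaluation, reconcile the sentence on existing control X-rays with the statements that EOS images are used, by stating which device produced the control images and when.
2. Record imaging device and image date for every knee in both groups.
3. Where matching on gender and prosthesis type allows, prefer controls who already have postoperative EOS images among the 165 revisions available.
4. Report HKA, mLDFA, mMPTA and aPPTA restricted to EOS-imaged knees beside the all-controls comparison. Do not attribute to CAS a difference that appears only when devices are mixed. Since the restricted set is smaller, judge this on estimates and intervals as well as p-values.
5. Do not add new EOS imaging of controls at the CT visit.

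The cost is a change of wording and two recorded variables. The downside is fewer controls, by a number the documents do not allow one to predict, and possibly looser matching in the EOS-only secondary comparison.

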### Sample size

The hypothesis is that the use of CAS leads to fewer outliers in prosthetic alignment compared to the use of mechanical alignment guides during rTKA. Primary outcome measure will be rotational prosthetic alignment. When using the conventional operation technique, around 25% of the knees is considered a radiological outlier. Therefore, a P2 value of 0.75 was chosen [21,36]. Previous research has shown that the use of CAS in TKA decreases the number of outliers by 17-30% [21,37,38]. When a 20% decrease in outliers is expected in the CAS group compared to the control group with P1 = 0.95, P2 = 0.75, power = 80% and alpha = 0.05, 44 patients per group are needed.

Since 2008 a total of amount of 21-30 rTKAs have been performed each year at UMCG, and an increase is expected. As a result of that, the possibility is expected of including 44 patients in the intervention group between September 2012 and September 2015. Inclusion of 44 patients in the historical control group is not expected to be a problem, as 165 rTKAs were performed between January 2002 and April 2012.

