### Study population

The study will be conducted at the Orthopedic Department of UMCG. Inclusion criteria for the intervention group are:

– Use of CAS during rTKA.

– Minimum age of 18 years.

– Total revisions, re-implantations and partial revisions of either the tibial or the femoral part are included. For partial revisions, only measurements of the part of the prosthesis to be revised will be used.

Inclusion criteria for the historical control group are:

– rTKA without the use of CAS.

– Minimum age of 18 years.

– Total revisions, re-implantations and partial revisions of either the tibial or the femoral part are included. For partial revisions, only measurements of the part of the prosthesis that was revised will be used.

– Patients will be included if the NexGen® revision system (Zimmer Inc., Warsaw, Indiana, USA) was used.

Exclusion criteria for both groups are:

– Insert replacements and placement of a patellar button only.

– Patients who receive a tumor prosthesis during rTKA.

– Patients with a limited knowledge of the Dutch language or who are mentally incapable of participating.

In both the intervention group and the historical control group the anesthetic, analgesic and postoperative physiotherapy protocols are identical.

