### Statistical analysis

All statistical analyses will be performed using the PASW software package (version 19, SPSS, Chicago, USA). Descriptive statistics will be used to describe the main characteristics of both research groups. Differences in rotational, coronal and sagittal alignment between the groups will be determined by using the nonparametric Mann-Whitney U-test for independent samples. For the clinical parameters, t-tests will be used for continuous values or the Mann-Whitney U-test when the variables are not normally distributed. A Chi-square test and a Fisher’s Exact test will be used for dichotomous values. For all test procedures, a p-value of < .05 will be considered to indicate statistical significance.

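### The rotational primary outcome is two angles with no success rule, so 44 per group, sized for one test on complete data, does not secure both 5% error and 80% power

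*Protocol article*

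**What the plan says.** All references are to the protocol article.

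- **Sample size** names one outcome: "Primary outcome measure will be rotational prosthetic alignment". The calculation is for one binary comparison: "P1 = 0.95, P2 = 0.75, power = 80% and alpha = 0.05, 44 patients per group are needed". The control rate behind it is that "around 25% of the knees is considered a radiological outlier".
- **Radiographic evaluation** splits the outcome: "rotation of the femoral and tibial components will be determined separately according to the Berger CT protocol". The femoral angle is defined as "Condylar twist angle for rotation of the femoral component: angle between the epicondylar axis and the prosthetic posterior condylar axis". The tibial angle has a different reference axis and its own normal value: "Normal rotation of the tibial component is considered 18° endorotation". Each has its own 3° outlier rule.
- **Statistical analysis** sets one threshold throughout: "For all test procedures, a p-value of < .05 will be considered to indicate statistical significance".
- **Study population** admits revisions of the tibial or femoral part alone, in both groups. For the intervention group it says "For partial revisions, only measurements of the part of the prosthesis to be revised will be used", and the control group has the equivalent rule.

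The article does not merge the two angles into one result per knee, does not rank them, and does not say whether one or both must differ between groups.

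**The concern.** A calculation for one test at 0.05 on 44 evaluable knees per group is attached to an outcome that produces two tests at 0.05, each on the knees that happen to have that component revised. Without a success rule, a report could claim the primary result on whichever angle reaches significance, at more than the stated error rate. If instead both angles are required, the study is smaller than it needs to be. Under either rule, each partial revision of the other component removes a knee from an angle whose power has no margin above 80%.

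Rotational alignment is the question that the article presents as not yet investigated, so how a positive primary result is defined matters for what the study can claim.

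**Working it through.** **Inputs.** Non-outlier proportions 0.95 and 0.75, alpha 0.05, power 80% and 44 per group come from Sample size. The two angles come from Radiographic evaluation, and the 0.05 threshold for each test from Statistical analysis. Assumed: two-sided tests, and the same 5% versus 25% outlier rates for each angle. The share of partial revisions is not given, so a range is used.

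**1. The plan's own figure.** Arcsine formula: h = 2·asin(√0.95) − 2·asin(√0.75) = 0.596, and n = 2·((1.960 + 0.842)/h)² = 44.17. Power at 44 is 79.8% by the same formula. Exact enumeration of both binomials with the uncorrected chi-square test gives 80.4%. The 44 reproduces, for one test with 44 evaluable knees per group.

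**2. If either angle may succeed.** Family-wise error for two independent tests is 1 − (1 − 0.05)² = 9.75%. With bivariate normal test statistics it is 9.1% at correlation 0.5 and 7.0% at 0.9. The chance of at least one significant angle, if both effects are real and independent, is 1 − (1 − 0.804)² = 96%.

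**3. If both angles must succeed.** The error rate stays within 5%. Joint power under independence is 0.804² = 65%. Positive dependence raises this, but it can reach 80.4% only if the two results always agree.

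**4. Loss of knees to partial revisions.** If a fraction f of revisions is partial, split evenly between components, each angle is available in 44·(1 − f/2) knees. For f = 20% that is 39.6 (about 40); for f = 40% it is 35.2 (about 35).

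Exact chi-square power per angle:

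| Evaluable knees per group | alpha 0.05 | alpha 0.025 |
|---|---|---|
| 44 | 80.4% | 69.7% |
| 42 | 78.4% | 66.9% |
| 40 | 76.3% | 63.9% |
| 35 | 70.3% | 59.9% |

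**5. Power per angle under Holm.** If only that angle's effect is real, power is roughly the alpha 0.025 figure: about 70% at 44 and 60% at 35. If both effects are real and independent, an angle is rejected when its p-value is below 0.025, or when it lies between 0.025 and 0.05 and the other is below 0.025:

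- 44 knees: 0.697 + (0.804 − 0.697)·0.697 = 77%
- 35 knees: 0.599 + (0.703 − 0.599)·0.599 = 66%

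**The case against.** **Do both properties fail at once?** A reader might infer that neither the 5% nor the 80% holds. The article does not support that, because it states no success rule. With 44 evaluable knees, the either-angle rule raises the error but leaves about a 96% chance of at least one significant angle. The both-angles rule lowers joint power but keeps the error within 5%. What stands is that each rule loses one of the two.

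**Is the number below 44 certain?** No. Partial revisions are allowed, but their share is unknown. Sample size also cites 165 historical procedures and 21–30 per year, so 63–90 over three years; more evaluable knees may exist. The stated target is nevertheless 44 patients, not 44 per angle.

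**Could the statistical analysis plan settle it?** It could name a single primary angle or add a multiplicity rule. The article itself, however, fixes 0.05 for every test and a sample size for one test. A later alpha split would not restore 80% per angle at 44.

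**Two further readings are tempting but unsupported.**

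- Fisher's exact test would have only 69.5% power at 44. The article lists it with chi-square for dichotomous values, after the clinical parameters, and assigns alignment to the Mann-Whitney test. Nothing makes Fisher the primary test. That power was computed for proportions while alignment is tested by ranks is a separate point.
- If 25% and 5% are knee-level rates over two independent components, each component is at 13.4% versus 2.5%, and power at 44 falls to 53%. This depends on what the cited sources counted, which cannot be seen here, and on independence.

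**Conclusion.** The point holds in a limited form. The arithmetic behind 44 is sound, but it applies to one test on complete data, and the primary outcome as defined is two tests on possibly incomplete data with no stated way to win. Either the family-wise error rises to between 7.0% (correlation 0.9) and 9.75% (independence), or joint power falls to about 65% under independence. Only near-perfect agreement between the two angles with no missing angle would preserve both stated figures, and nothing in the article suggests that. Separately, power per angle drops to about 76% at 40 knees and 70% at 35. These counts rest on assumed partial-revision shares of 20% and 40%, evenly split. All power figures assume the planning rates apply to each angle.

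**What to change.** Name one primary endpoint, tested once at 0.05, and make the other rotational results secondary. Two choices work.

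- **A knee-level outlier:** at least one revised component more than 3° from its target. This fits the per-knee wording of the planning rate and keeps every partial revision in the count. Total revisions have two chances to be an outlier and partial revisions one, so stratify the comparison by total versus partial revision, or report it for each. To illustrate, with 13.4% outliers per component, independence and no treatment effect, a group with no partial revisions would show 1 − 0.866² = 25%. A group with 40% partial revisions would show 0.6·25% + 0.4·13.4% = 20%. The article matches on gender and prosthesis type, which does not remove this.
- **One named angle:** simpler, but its power depends on how many knees had that component revised, and that number should be stated.

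Alternatively, keep both angles as primary with Holm. Restate power per angle as about 70% (only that effect real) to 77% (both real, independent) with 44 evaluable knees, and about 60–66% with 35.

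The change is to wording. No extra patients are needed; the price is a less favourable stated power where both angles stay primary or a single angle loses knees.
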